#### Power Analyses

Power analyses were performed before recruitment to estimate the sample size needed based on the HbA1c level as the primary outcome. Given an effect size of 0.35, a significance level of 5%, a standard deviation of the outcome variable of 0.5, statistical power of 80%, and a two-tailed significance test, the sample size was estimated to be 34 individuals in each group. To compensate for dropouts, the sample was set to 50+50 (two intervention groups), and 50 in the control group. A total of 151 patients were included.

### Evaluation Measures

#### Overview

Our evaluation is based on the Model for Assessment of Telemedicine (MAST), which is a framework developed for the evaluation of the TM interventions in RENEWING HEALTH [39]. We are also using principles from the complex intervention framework developed by the Medical Research Council in the United Kingdom [52]. We intend to evaluate a large number and variety of outcomes. The consolidated standards of reporting trials (CONSORT) statements for reporting parallel group randomized trials are followed [53,54]. The study data include responses on self-reported questionnaires, logs from the Few Touch application, and data collected from patient journals obtained from the GPs. To assess the representativeness of the sample, we will use data from the general population with and without diabetes from the Nord-Trøndelag Health Study (HUNT 3) in Norway [55]. We will also conduct in-depth interviews with patients and health care providers consecutively. In addition, we will collect data from the technical support service to get knowledge about who are using the service, frequency of use, and what they are asking for. Further, we collect notes from the diabetes nurse taken during the health counseling. The measures in our study are described in detail below.

#### Demographics

These are self-reported measures and include age, sex, education, cohabitation, marital status, and working status of the participant.

#### Clinical Measures

Data from the medical records include medication, dosage, treatment period, and adjustments during the study period. Data about height, weight, blood pressure, and waist circumference are also obtained from medical records. Biological data include HbA1c and lipid levels. Frequency of hypoglycemia and comorbidities are self-reported, and late complications such as atrial fibrillation, intermittent claudication, cerebrovascular disease, coronary disease, and microalbuminuria are obtained from the GPs.

### Primary Outcome Measure

The primary outcome is the difference between the control group and the intervention groups regarding change in HbA1c level after 4 months and after 1 year. When possible, HbA1c levels are recorded within 2 weeks before or after the expected date of follow-up (ie, within a 1-month window) [56]. HbA1c level has been shown to vary between 100 laboratories in the United Kingdom and between the various HbA1c assays in use [57]. In the present study, patients are included from different GP offices, and there may be variations in HbA1c levels recorded. To avoid bias potentially introduced through the use of different HbA1c assays, the DCA Vantage Analyzer from Siemens is used when possible.

### Secondary Outcome Measures

#### Short Form-36 for Measuring Health-Related Quality of Life

This questionnaire contains eight conceptual domains within physical functioning and mental health giving scores of 0-100: (1) physical functioning, (2) role-physical, (3) bodily pain, (4) general health, (5) vitality, (6) social functioning, (7) role-emotional, and (8) mental health [58,59]. It is one of the most frequently applied surveys for measuring health-related quality of life, and its domains are relevant for people with diabetes [60]. The Short Form-36 (SF-36) was included in RENEWING HEALTH to allow comparisons between different regions included in the project and to allow comparisons with norms.

#### Center for Epidemiological Studies Depression Scale for Measuring Depression

The Center for Epidemiological Studies Depression Scale is a tool for measuring depressive symptoms, but not for diagnosing depression [61]. It assesses the behavioral, cognitive, and affective symptoms of depression, and measures sleep disturbance and loss of appetite, which can be important signs of depression and may have major impact on diabetes management.

### Behavior Change and Empowerment

#### Health Education Impact Questionnaire (heiQ)

The Health Education Impact Questionnaire (heiQ) contains 40 questions to measure the effectiveness of patient education and self-management interventions for people with chronic conditions, as well as the patients’ health competence. It is an eight-scale questionnaire with the following domains: (1) positive and active engagement in life, (2) health-directed behavior, (3) skill and technique acquisition, (4) constructive attitudes and approaches, (5) self-monitoring and insight, (6) health service navigation, (7) social integration and support, and (8) emotional well-being. The instrument has been proven to be valid and reliable [62]. The instrument has recently been translated to Norwegian, and a psychometrically testing is ongoing.

#### Diabetes Empowerment Scale-Short Form

The Diabetes Empowerment Scale-Short Form (DES-SF) has eight items related to managing the psychosocial aspects of diabetes, and measures readiness to change and achieve goals [63,64]. The DES-SF has been proven to be valid and reliable, although the short form has not been through a test-retest validation [65]. This instrument has been translated into Norwegian for the present study.

#### Physical Activity

Measures of physical activity are collected by the same questions as in the HUNT 3 study for comparison purposes with a diabetes sample from the general population. We have also included one question based on the transtheoretical stages of change to assess the respondents’ motivation toward physical activity and change in activity level [66].

#### Nutritional Habits

Measures of nutrition are collected using the same questions as those used by the Cancer Registry of Norway in the Norwegian Colorectal Cancer Prevention study, which collects data about the intake of fruit, vegetables, and fat [67]. Motivation for changing nutritional habits is assessed using a question based on the transtheoretical stages of change [46].

### Patient Acceptability

#### Measurement of the Usability of the Mobile Self-Management Tool

The usability of the mobile self-management tool FTA Touch application will be measured by the System Usability Scale (SUS) that comprises 10 items to provide a global view of the patients’ subjective assessment of usability. The SUS has been found to be a “valuable and robust tool in helping assess the quality of a broad spectrum of user interfaces” [68]. The measure has been used earlier in Norway [50].

#### Assessment of the Patients’ Perceptions

To assess the patients’ perceptions about the mobile self-management tool Few Touch application, the patient acceptance questionnaire, Service User Technology Acceptability Questionnaire, used in the Whole Systems Demonstrator program [69] is used in all pilot studies of RENEWING HEALTH. This questionnaire contains 22 items within the following domains: utility of the kit, effect on health status, effects on access to care, effects on health care/social care, privacy, suitability of the kit, and satisfaction with the kit.

#### Patients’ Experiences With the Intervention

We are also integrating a qualitative evaluation with in-depth interviews of consecutive patients at the end of the study. We are using grounded theory [70] and have developed a semistructured interview guide to obtain patients’ experiences and their degree of satisfaction with the intervention. Integrating a qualitative approach into this RCT may strengthen the description of its effects. The interviews will be conducted by a researcher who had no earlier contact with the patients. The interviews will continue until saturation of data is achieved.

### Health Care Perspectives

Health Care perspectives will be collected through semistructured interviews with health care professionals, doctors, and nurses in the GP offices and the diabetes outpatient clinics involved in this study. The focus for this evaluation will be facilitators for and obstacles to using the system provided or similar systems.

### Cost-Effectiveness

The objective of the economic study is to analyze whether the interventions in addition to standard care are cost effective compared to standard care alone. The study will be conducted from a societal perspective; all costs and consequences falling on the health service as well as on the patient and their employers will be included. The analysis will include data on investments in the TM app, as well as training costs, cost of maintenance, and technical support. Data on health resource use (such as GP visits, hospital admissions, and contacts with nurses), transportation costs, and costs of foregone production are also collected. Market prices, tariffs, and average wages (including employment costs) will be used as cost weights or unit costs and will be presented alongside resource data. Total costs of the treatment arms will be compared with the benefits of improving the patients’ health. Health benefits will be measured in quality-adjusted life years (QALYs). Patient-specific QALYs will be computed from the SF-36 Health Survey by employing an estimated preference-based algorithm developed by Brazier et al [71]. QALYs will be calculated by using under the curve analysis, with linear interpolations between utility scores collected at baseline, 4 months, and 12 months assessments. Incremental cost per QALY will then be calculated and incremental cost-effectiveness ratios will be reported and presented on the cost-effectiveness plane [72].

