**Conclusions:**

The key goals of this trial are to investigate the effect of an electronic diabetes diary app with and without health counseling, and to determine whether health counseling is important to the continued use of the application and the patients’ health competence and acceptability. Research within this area is needed because few studies have investigated the effectiveness of apps used in long-term interventions with this degree of self-management.

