
### Aim of the Study

The present study is the Norwegian part of the European Union (EU) Collaborative Project—REgioNs of Europe WorkINg together for HEALTH (RENEWING HEALTH). The aim of this study is to validate and evaluate innovative TM tools on a large scale using a common evaluation method, thereby making it easier for decision makers to choose the most efficient and cost-effective technological aids [39]. The Norwegian study evaluates whether the introduction of personalized and technology-supported self-management with and without health counseling intervention produces benefits in desired outcomes, as reflected in HbA1c level, health-related quality of life, behavior change, and cost-effectiveness.

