### Development of the Intervention

#### Overview

All participants receive usual care by their GP. The patients in the control group receive only usual care. Usual care in Norway is regulated by national guidelines, which include at least one annual visit to a GP. Standard measurements are blood pressure, serum concentrations of lipids and glucose, HbA1c level, and weight and body mass index. The patient’s regular visit with a GP includes treatment for elevated blood glucose, blood pressure, and lipids when needed. The GP also emphasizes the importance of lifestyle changes [8].

There are two intervention groups (I+II) in our study. In addition to usual care, the participants in both the intervention groups receive a mobile phone with the diabetes diary app referred to as the Few Touch application, which is a self-help tool comprising five elements that are accessible to the user: (1) food habits registration system, (2) blood glucose data management system, (3) physical activity registration system, (4) personal goal-setting system, and (5) general information system. Blood glucose data are transferred automatically to the mobile phone-based diabetes diary from the blood glucose meter when the user has performed a measurement. Activity data and food habits are entered manually by the user. The users can also set personal goals for physical activity and food habits, access related tips, and look up words and concepts related to their disease.

In addition to the mobile phone, intervention group II also receives theory-based health counseling delivered by a diabetes specialist nurse working at a diabetes outpatient clinic at a university hospital, and with the possibility of support from a dietitian. The health counseling intervention comprises five modules (Table 1) and is delivered over 4 months immediately following the randomization. The nurse sends standardized short messages (using short message service, SMS) a few days before calling to inform the patients of the planned content in the phone conversation. The patients are also able to initiate SMS text messaging to communicate with the diabetes specialist nurse.

**Table 1 table1:** Five modules of the health counseling intervention.

Module	Module theme
Module 1 (intro)	Introduction
Module 2 (1st month)	Living with diabetes
Module 3 (2nd month)	Goal setting
Module 4 (3rd month)	Diet and physical activity
Module 5 (4th month)	Looking back and continuing forward

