## Results

The inclusion of patients started in March 2011, and 100% of the planned sample size is included (N=151). Of all the participants, 26/151 patients (17.2%) are lost to follow-up by now, and 11/151 patients (7.3%) are still in the trial. Results of the study protocol will be presented in 2014. The aim of this study is to validate and evaluate innovative TM tools on a large scale through a common evaluation, making it easier for decision makers to choose the most efficient and cost-effective technological interventions.

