## Discussion

Despite a large number of studies of TM and systematic reviews of the effects of TM, there remains a lack of consensus in research findings [28]. The key elements in this trial are the effect of an intervention that combines a mobile self-management tool with motivational support and the comparison with an intervention comprising TM alone. It is of interest to investigate the effect of the TM application with and without health counseling, and it is reasonable to question whether health counseling is important for the continued use of tools such as those in this study and for patients’ health competence and acceptability. One might question whether the health counseling part of the intervention will motivate the patients or whether the repeated phone calls from the diabetes nurse will become more tiresome than supportive and thus unwanted. Research on this question is needed, but to our knowledge, no studies have investigated this thoroughly.

We have chosen to include adult patients of all ages and some not familiar with mobile phones. Our qualitative approach will allow us to search for possible limitations in the use among different groups of patients. This may give us valuable knowledge about how to encourage the use among different groups of patients and how to assess the effects of a low-intensity intervention on different subgroups. Our qualitative approach might also reveal important information in discussions with patients and health personnel about how to integrate self-management tools in the health care system.

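### The stated economic objective sets the interventions against standard care and names no contrast of app plus counseling with app alone, so group II's ratio can mislead on whether counseling is worth adding

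*Protocol article*

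**What the plan says.** The Cost-Effectiveness section gives the economic objective as to "analyze whether the interventions in addition to standard care are cost effective compared to standard care alone". It then says that "Incremental cost per QALY will then be calculated and incremental cost-effectiveness ratios will be reported and presented on the cost-effectiveness plane". That second sentence names no comparator. The section also says that total costs of the arms will be compared with the health benefits. The cost-effectiveness paragraph under Statistical Analysis promises means and 95% confidence intervals for resource use, total costs and effectiveness, again without naming a contrast. The post hoc comparisons between the three groups in that section are specified for the main outcome, HbA1c.

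The arms are nested. Everyone receives usual care, both intervention groups receive the app, and "In addition to the mobile phone, intervention group II also receives theory-based health counseling delivered by a diabetes specialist nurse" (Development of the Intervention, Overview).

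On purpose, Aim of the Study asks whether "personalized and technology-supported self-management with and without health counseling intervention produces benefits in desired outcomes" and lists cost-effectiveness among those outcomes. It describes the wider aim as "making it easier for decision makers to choose the most efficient and cost-effective technological aids". The Discussion names as key elements the effect of an intervention that "combines a mobile self-management tool with motivational support and the comparison with an intervention comprising TM alone".

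**The concern.** A health service can give a patient one of three packages: usual care, app, or app plus nurse counseling. With more than two mutually exclusive options, the informative ratio for each is taken against the next less costly option that is not dominated. If both packages are set against usual care, group II's ratio blends what the app achieves with what counseling achieves. A cheap and effective app can make the combined package look good value even when counseling adds little for its cost. The reverse can also happen: a favorable ratio for the app alone can draw a reader away from the package with the higher net benefit.

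At stake is the economic reading of the contrast between groups II and I, the contrast for which the trial has a separate counseling arm. The HbA1c analysis is not affected.

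**Working it through.** **Inputs.** The comparator is from Cost-Effectiveness and the nested arms are from Development of the Intervention. The protocol gives no costs, utilities or QALY gains, so there is no economic figure of its own to reproduce. All costs and QALYs below are assumed.

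**Identity.** Let C1 and Q1 be the incremental cost and QALYs of app versus usual care, and C2 and Q2 those of app plus counseling versus usual care.

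- App versus usual care: R1 = C1/Q1
- App plus counseling versus usual care: R2 = C2/Q2
- App plus counseling versus app: R21 = (C2 − C1)/(Q2 − Q1)

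Since C1 = Q1·R1 and C2 − C1 = (Q2 − Q1)·R21,

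R2 = [Q1·R1 + (Q2 − Q1)·R21] / Q2.

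When Q1 and Q2 − Q1 are both positive, this is a weighted average of R1 and R21 with QALY weights. R2 alone does not determine R21.

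**Illustration 1 (assumed).** C1 = 1, Q1 = 0.020; C2 = 3, Q2 = 0.030.

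- R1 = 1/0.020 = 50
- R2 = 3/0.030 = 100
- R21 = (3 − 1)/(0.030 − 0.020) = 200
- Identity: (0.020 × 50 + 0.010 × 200)/0.030 = 3/0.030 = 100

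Net benefit against usual care is threshold × QALYs − cost:

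| Threshold | App | App plus counseling | Better |
|---|---|---|---|
| 150 | 150 × 0.020 − 1 = 2.0 | 150 × 0.030 − 3 = 1.5 | App |
| 250 | 250 × 0.020 − 1 = 4.0 | 250 × 0.030 − 3 = 4.5 | App plus counseling |

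At 150 both packages pass against usual care. A reader who takes the more effective passing option chooses wrongly, and one who takes the lowest ratio chooses rightly. At 250 the lowest-ratio reader chooses wrongly.

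**Illustration 2 (assumed).** Hold app plus counseling versus usual care at C2 = 1,500 and Q2 = 0.05, so R2 = 30,000 throughout, and vary the app's share:

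| C1 | Q1 | R1 | R21 |
|---|---|---|---|
| 300 | 0.005 | 60,000 | 1,200/0.045 = 26,667 |
| 500 | 0.020 | 25,000 | 1,000/0.030 = 33,333 |
| 500 | 0.030 | 16,667 | 1,000/0.020 = 50,000 |
| 500 | 0.040 | 12,500 | 1,000/0.010 = 100,000 |
| 500 | 0.045 | 11,111 | 1,000/0.005 = 200,000 |

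One ratio of 30,000 against usual care is compatible with counseling costing from about 27,000 to 200,000 per QALY. In the first row the app is extendedly dominated (60,000 exceeds 26,667), so the next non-dominated comparator for group II is usual care and 30,000 is the right figure. The direction of any distortion therefore cannot be known in advance.

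**The case against.** **The sentence is only a statement of purpose.** The sentence on incremental ratios names no comparator and does not exclude II versus I. This stands. A reader might infer that the plan limits itself to standard care, but the text does not say so. The supportable statement is that standard care is the only economic comparator named.

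**Dominance rules, thresholds and acceptability curves belong in a fuller plan.** This also stands, and their absence is not the point. The comparator is different: the article states it, and states it too narrowly for three nested options.

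**The counseling question is not posed in cost terms.** The abstract's Conclusions give the goal as "to determine whether health counseling is important to the continued use of the application and the patients’ health competence and acceptability", and the Discussion uses similar endpoints. The aim of helping decision makers belongs, in the abstract, to the European project as a whole. So one cannot say that the value for money of counseling is the trial's declared key question. The economic link rests on Aim of the Study, which lists cost-effectiveness among the outcomes with and without counseling, together with the Discussion's emphasis on the comparison with the app alone. That is enough to make the contrast relevant.

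**The information would not be lost.** If mean costs and QALYs are reported by arm, a reader can subtract them, obtain a II-versus-I point estimate, and see whether group I dominates group II. This is correct. What cannot be recovered is the joint uncertainty, because separate intervals for costs and for effects do not show how the two vary together.

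**Conclusion.** The concern holds in a limited form. The stated objective leads to a ratio for group II that does not identify what counseling adds, and no other economic contrast is named. The averaging result is algebra and needs only that both QALY gains are positive.

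The size is unknown, because every cost and QALY figure above is assumed. In the illustrations, counseling's own ratio ran from slightly below the figure against standard care (26,667 against 30,000) to more than six times it (200,000).

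Two stronger readings are not supported. A reader might infer that the trial cannot show the value of counseling; the data are collected and a point estimate is derivable, so the gap is in the planned comparison and its uncertainty. A reader might also infer that every threshold between 100 and 200 in the first illustration gives the wrong choice; it can do so, but that depends on the decision rule, which the protocol does not state.

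**What to change.** Reword the objective in Cost-Effectiveness as a full incremental analysis of the three arms: order them by mean cost, remove dominated and extendedly dominated options, and compare each remaining option with the next. Report app plus counseling versus app alone (or versus the next non-dominated option) with its uncertainty, for example as incremental net benefit over a range of thresholds. Keep the ratios against standard care as supplementary results.

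The cost is a change of wording and one more contrast. Resource use, including nurse contacts, and SF-36 utilities are already planned. The drawback is precision: the trial was sized on HbA1c with about 50 patients per arm, so the interval for the counseling increment will be wide. It should be reported with that caveat.

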### Statistical Analysis

Baseline measurements will be presented using descriptive statistics. The participants will be block randomized, and the groups should therefore be equal in age and gender distribution. The groups will be compared with regard to clinically relevant variables to ensure they are comparable. Because of the limited size of the groups, they may differ on some variables and, when such variables are identified, they will be adjusted for in the statistical analyses, for example, by treating them as possible confounders.

Baseline data will be compared with data from the normal population (HUNT 3 study) to assess whether our sample is representative of the entire population of Norwegian individuals living with diabetes.

The differences in the main outcome between baseline and 4 months and between baseline and 1 year will be compared between the three groups. First, the crude difference will be analyzed using analysis of variance with post hoc tests (differences between groups). The difference between baseline and the following two measurements within each group will be analyzed using a *t* test. When a change in a selected outcome variable is identified, this change will be modeled using linear regression adjusted for possible confounders.

The cost-effectiveness data will be analyzed using standard statistical analyses depending on the distribution of the data. Missing values will be replaced by imputation. Mean values and 95% CI will be reported for each component of resource use as well as for total costs and effectiveness. Sensitivity analyses will be conducted to handle nonsampling variation.

Our study has a longitudinal design and we expect some dropouts. Therefore, we will perform two analyses: one based on intention to treat and another based on the participants who actually participated actively in our study (per protocol).

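### Adjustment of the incremental QALY for baseline utility is not pre-specified but depends on an imbalance being noticed, so smaller imbalances carry through and precision is lost

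*Protocol article*

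**What the plan says.** Protocol article, Cost-Effectiveness, fixes how each patient's QALY is built. The utility comes from the SF-36: "Patient-specific QALYs will be computed from the SF-36 Health Survey by employing an estimated preference-based algorithm". The QALY is then the area under a curve, "with linear interpolations between utility scores collected at baseline, 4 months, and 12 months assessments". The next step is the comparison of arms: "Incremental cost per QALY will then be calculated and incremental cost-effectiveness ratios will be reported and presented on the cost-effectiveness plane". No covariate is named.

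Protocol article, Statistical Analysis, says of the economic outcomes: "The cost-effectiveness data will be analyzed using standard statistical analyses depending on the distribution of the data". Baseline utility is not mentioned there either. The sensitivity analyses promised for the economic data concern variation other than sampling variation, so they do not cover chance imbalance.

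The same section opens with a general rule on covariates. Groups are compared at baseline on variables of clinical relevance, and because the groups are small, "they may differ on some variables and, when such variables are identified, they will be adjusted for in the statistical analyses". The rule lists no variables, gives no criterion for calling a variable different, and is not tied to the QALY analysis.

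**The concern.** A QALY built this way contains the baseline score, and the later scores are correlated with it. If the arms happen to differ in utility at the start, part of that difference reappears in the incremental QALY, although treatment cannot have caused it. A rule that adjusts only after an imbalance has been identified leaves two gaps. Imbalances too small to be identified still carry through. The gain in precision from the covariate, which exists even when the arms are perfectly balanced, is taken up only by accident. The choice of estimator also stays open until the baseline data have been seen.

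The incremental QALY is the denominator of the cost-effectiveness ratio, and cost-effectiveness is among the outcomes named in the study's aim, which is to inform decision makers. Noise in that denominator that could have been removed matters for this purpose.

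**Working it through.** **Plan's own figures.** The economic analysis has no numerical target to reproduce. The arm size comes from the HbA1c calculation: a difference of 0.35, SD 0.5, two-sided 5% and 80% power give 33.02 per group by the t test. Rounded up, this is the stated 34, which was then raised for dropout: "the sample was set to 50+50 (two intervention groups), and 50 in the control group". I use 50 per arm.

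**Assumptions, not in the documents.** Utility SD s = 0.10 to 0.15, equal at all visits. A common between-visit correlation r = 0.4, 0.6 or 0.8.

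**Step 1: weights of the three scores.** With visits at 0, 4 and 12 months and the area in years:
- baseline: (4/12)/2 = 1/6
- 4 months: (4/12)/2 + (8/12)/2 = 1/2
- 12 months: (8/12)/2 = 1/3

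**Step 2: pass-through.** A baseline difference d between two arms moves the unadjusted QALY difference by d × (1/6 + (5/6)r). Only the 1/6 comes from the baseline point itself. The rest comes through the correlated later scores.

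**Step 3: share of QALY variance explained by baseline.**
- Variance of the QALY in units of s²: sum of squared weights 14/36, plus r × 22/36 for the cross-products.
- R² = (1/6 + 5r/6)² / (14/36 + 22r/36).
- Ratio of adjusted to unadjusted interval width: √(1 − R²).

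| r | Pass-through | Variance / s² | R² | Width ratio | Narrowing |
|---|---|---|---|---|---|
| 0.4 | 0.50 | 0.633 | 0.39 | 0.78 | 22% |
| 0.6 | 0.67 | 0.756 | 0.59 | 0.64 | 36% |
| 0.8 | 0.83 | 0.878 | 0.79 | 0.46 | 54% |

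**Step 4: size of a chance imbalance.** Its standard error is s × √(2/50) = 0.2s, which is 0.020 at s = 0.10 and 0.030 at s = 0.15. A one-standard-error imbalance therefore shifts the QALY difference by 0.020 × 0.50 = 0.010 at the low end and 0.030 × 0.83 = 0.025 at the high end. The part due to the baseline point alone is 0.020/6 = 0.003 to 0.030/6 = 0.005.

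**Step 5: what the conditional rule could miss.** The plan does not define when a variable counts as different. If the criterion were a 5% test (an assumption), then at s = 0.10 a difference of up to 1.96 × 0.020 = 0.039 would go unadjusted. That carries 0.039 × 0.50 = 0.020 to 0.039 × 0.83 = 0.033 QALY.

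**Step 6: precision at s = 0.10.** The standard error of the incremental QALY is 0.020 × √(variance / s²), multiplied by the width ratio after adjustment. It falls from 0.0159 to 0.0124 (r = 0.4), from 0.0174 to 0.0112 (r = 0.6) and from 0.0187 to 0.0086 (r = 0.8).

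**The case against.** The strongest reply is that the article chooses no wrong estimator. Regression on baseline utility is a standard analysis and fits the wording on economic data. The general rule is not confined to HbA1c and could include utility. This is a condensed article, and a fuller plan may name the model. Much of this stands: the point concerns a method that could be better, not a demonstrated error. But the article does state a covariate rule of its own, and that rule is data-dependent. A fuller plan that always adjusts would depart from it, and the two would need reconciling.

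A reader might also infer more than the documents support:

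- **That baseline utility is not adjusted for at all.** The general rule may bring it in if it is found to differ. What is missing is a commitment to adjust whatever is found.
- **That the incremental QALY is biased.** Over randomizations the unadjusted difference is unbiased, and chance imbalance is part of the sampling error that its confidence interval already reflects. The harm is error given the imbalance in this trial, and an interval wider than it need be.
- **That starting the curve at baseline is the mistake.** That construction is conventional. Most of the carry-over arises from correlation with later scores and would affect any unadjusted comparison of follow-up utilities.
- **That missing values will be filled in once, giving intervals that are too narrow.** The text says only "Missing values will be replaced by imputation", which fits multiple imputation equally well.
- **That imbalance would reverse the sign of the ratio or match the expected benefit.** The documents give no expected QALY gain, so there is nothing to compare the shift with.

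**Conclusion.** The point holds as a worthwhile improvement to a secondary analysis. Whether the incremental QALY is adjusted for baseline utility is left to an undefined judgement of imbalance, and always adjusting is better than that rule whether or not the arms turn out balanced. The pass-through and the gain in precision depend only on the assumed correlation and on equal SDs across visits. The shift in QALY units also depends on the assumed utility SD. None of these values is in the documents, so the ranges show the order of magnitude and do not predict this trial. The trapezoid weights rest on the stated visit times alone. The gain in precision is for the incremental QALY. How far the ratio itself would change cannot be worked out without cost data.

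**What to change.** State in Statistical Analysis that incremental QALYs, for each intervention arm against control, are estimated by regressing QALY on arm and baseline SF-36 utility in every case, whatever imbalance is observed. State also that these adjusted differences feed the cost-effectiveness ratio and the cost-effectiveness plane. Exempt baseline utility from the rule that adjusts only for variables found to differ. If a fuller plan already specifies this model, bring the article's general rule into line with it.

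The cost is a sentence or two of plan text and a few lines of code. The baseline SF-36 is already collected, so no new data are needed, and one extra covariate uses a single degree of freedom.
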